#### Qualitative interview study

Participants in Group 1 must meet the criteria for the cohort study, and must also have:

Completed the baseline and 6-month follow-up surveys of the longitudinal cohort study.Indicated in the baseline survey that they consent to be contacted for participation in further research.Provided data on whether or not they have heard of and/or used any staff support programmes.

Participants in Group 2 must:

Have been involved in implementing staff support programmes in one of the 18 participating Trusts or Nightingale hospitals.Be aged 18 years and over.Be able to give informed consent to take part in research.Be able to understand and communicate in English.

### Measures

#### Longitudinal cohort study

##### Baseline

The baseline survey will involve a short survey (5–10 min) which collects information on the following topics: (1) Contact details, (2) Occupational information (eg, occupational group, length of professional registration), (3) Sociodemographic characteristics, (4) Working practices (eg, access to PPE, performing aerosolising procedures), (5) Perceived support from managers, colleagues, friends and family, (6) COVID-19-related questions (eg, suspected infection status, COVID-19 test status, isolation/quarantining), (8) Staff support programme access, (9) Self-reported diagnosed health conditions and (10) Common mental disorders. The prevalence of probable common mental disorders will be assessed using the 12-item GHQ-12, with a cut-off score of 4 or more indicating caseness.^13^

There will be the option for participants to complete an additional longer survey (10–15 min), which includes information on the following: (1) Impact of COVID-19 (eg, on family, income, health, positive and negative changes in personal life or work), (2) Work experiences (leadership and teamwork, sickness absence, unsafe clinical practices, preparedness), (3) Usefulness of staff support programmes, (4) Caring responsibilities outside of work, (5) Confidence in institutions to handle the COVID-19 pandemic. In addition, the following validated measures will be used in the longer survey: the 7-item Generalised Anxiety Disorder (GAD-7) Scale to measure probable moderate anxiety disorder with a cut-off score of 10 or more indicating caseness;^17^ the 9-item Patient Health Questionnaire (PHQ-9) to measure probable moderate depression with a cut-off score of 10 or more indicating caseness;^18^ the 10-item Alcohol Use Disorder Identification Test to measure alcohol consumption with a cut-off score of 8 or more indicating hazardous drinking;^19^ the PCL-6 civilian version to measure PTSD with a cut-off score of 14 or more indicating the presence of probable PTSD;^15^ the 9-item Moral Injury Event Scale (MIES) to measure moral injury, with a higher score indicating greater exposure to morally injurious events;^20^ the 14-item Warwick-Edinburgh Mental Well-being Scale (WEMWBS) to measure subjective well-being and psychological functioning, with a higher score indicating a higher level of mental well-being;^21^ the 6-item Brief Resilience Scale (BRS) to measure psychological resilience, with a higher score indicating a higher level of resilience;^22^ the 12-item Burn-out Assessment Tool (BAT) to measure burn-out, with a cut-off score of 3.02 indicating probable burn-out.^23^ All validated measures use Likert Scale response options.

We will also assess suicidal ideation in the longer survey, using items related to suicidal thoughts, suicide attempts and self-harm derived from the CIS-R.^14^ We will measure fatigue using three novel items exploring: (1) Emotional and physical exhaustion on a 0–10 scale; (2) Whether any experienced fatigue is greater than usual tiredness (yes/no); and (3) Whether any experienced fatigue interferes with the ability to do things (yes/no).

##### Follow-up—6 months

The 6-month survey will also involve a short version and long version. The short survey will collect information on the national and local staff support programmes used, and on household income. The same questions as at baseline will be asked regarding: COVID-19 experiences (eg, suspected infection status, COVID-19 test status, isolation/quarantining); teamwork; support from colleagues and friends/family. The same measures will be used in the 6-month survey as at baseline, as follows: GHQ-12, GAD-7, PHQ-9, Alcohol Use Disorders Identification Test (AUDIT), PCL-6, MIES and the CIS-R suicidality questions. In addition, the short form of the Post-traumatic Growth Inventory will be used.^24^

The long survey will collect the same measures as at baseline: WEMWBS, BRS, BAT, Fatigue. It will also collect information on the personal and occupational factors as at baseline. The topics covered may be updated as the pandemic evolves, in order to capture the most relevant information.

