### Analysis plan

#### Longitudinal cohort study

Response weights will be calculated for each Trust, generated using a raking algorithm based on age, sex, ethnicity and role (using Trust population data obtained from Human Resources), with missing demographic data imputed using multiple imputation (for the purposes of weighting only). Trusts with response rates under 5% will be dropped from the analysis. Representativeness of the sample will be described using frequencies and percentages, and descriptive statistics given for each variable to summarise participants (frequencies and weighted percentages for categorical variables, mean and SD for continuous variables). We will examine differences between participants completing only the short survey, compared with those completing both the short and long surveys. We will summarise the weighted prevalence of the primary and secondary outcomes, stratified by sociodemographic and occupational factors. We will explore potential longitudinal associations between sociodemographic characteristics and occupational factors with the outcome measures (eg, GHQ-12, GAD-7, PHQ-9, AUDIT, PCL-6, MIES). Three-level random intercept linear or logistic (depending on the distribution of the outcome) regression models will be used to account for the hierarchical structure of the data, considering observations from baseline, 6-month follow-up and 12-month follow-up at level 2 and NHS trusts at level 3. We will use a measure of pressure on Trusts as the key exposure (eg, ratio of beds in use to staff numbers, ie, those not on sick leave), plotting levels of this exposure over time (aggregated at the Trust level), before partitioning the data into meaningful periods corresponding to burden level over the baseline data collection period (April 2020 to January 2021). We will plot all measures over time to look at patterns between this exposure and outcome levels, and use three-level random intercept logistic and linear regression models, as appropriate, to explore factors associated with outcomes in each period.

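### GAD-7, PHQ-9, AUDIT, PCL-6, MIES and the suicidality items move from the optional long survey at baseline to the short survey at 6 months, so comparisons across waves can show false change if long-survey uptake depends on distress

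*Protocol article*

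**What the plan says.** All places are in the Protocol article.

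- **Measures, Longitudinal cohort study, Baseline (short survey).** GHQ-12 is the only named symptom scale: "The prevalence of probable common mental disorders will be assessed using the 12-item GHQ-12, with a cut-off score of 4 or more indicating caseness".
- **Same section (long survey).** The long survey is voluntary: "There will be the option for participants to complete an additional longer survey". It holds the other scales: "In addition, the following validated measures will be used in the longer survey: the 7-item Generalised Anxiety Disorder (GAD-7) Scale", followed by PHQ-9, AUDIT, PCL-6, MIES, WEMWBS, BRS and BAT. It also holds the suicidality items: "We will also assess suicidal ideation in the longer survey, using items related to suicidal thoughts, suicide attempts and self-harm derived from the CIS-R".
- **Follow-up—6 months.** The paragraph that describes the short survey continues: "The same measures will be used in the 6-month survey as at baseline, as follows: GHQ-12, GAD-7, PHQ-9", and goes on to AUDIT, PCL-6, MIES and the suicidality questions. The next paragraph gives the long survey a separate list: "The long survey will collect the same measures as at baseline: WEMWBS, BRS, BAT, Fatigue".
- **Follow-up—12 months.** Short and long versions are to be similar to those at 6 months, with room for refinement.
- **Study procedures, Data collection.** Everyone is followed up at each point unless they withdraw, whether or not they completed the previous survey.
- **Analysis plan, Longitudinal cohort study.** GHQ-12, GAD-7, PHQ-9, AUDIT, PCL-6 and MIES are given as example outcomes for three-level models "considering observations from baseline, 6-month follow-up and 12-month follow-up at level 2 and NHS trusts at level 3", and all measures are to be plotted over time. Weights are raked on age, sex, ethnicity and role. Imputation is confined to missing demographic data and serves only the weighting. Short-only participants are to be compared with those who completed both surveys.

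**The concern.** A participant who completed only the short survey at baseline has no baseline PHQ-9, GAD-7, AUDIT, PCL-6, MIES or suicidality value. The same person supplies all of these at 6 months by answering the short survey. The baseline and follow-up figures for these measures thus describe differently selected groups.

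If the decision to go on to the long survey is related to distress, the two groups differ in level even when nobody's health has changed. Distressed staff might be more willing to describe their difficulties, or too exhausted to carry on, so the direction is open.

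The Introduction presents the longitudinal data as the means of telling whether a surge of symptoms persists or remits, and the secondary objectives include patterns of distress over time. An artefact of a few percentage points could be read as either persistence or remission.

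**Working it through.** The article states no figure on this point, so there is nothing to reproduce. It gives neither long-survey uptake nor scores by survey type. Every numerical input below is an assumption.

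**Step 1. Placement by wave.**

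| Measure | Baseline | 6 months |
|---|---|---|
| GHQ-12 | short | short |
| GAD-7, PHQ-9, AUDIT, PCL-6, MIES, suicidality | long (optional) | short |
| WEMWBS, BRS, BAT, fatigue | long (optional) | long |

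Only the middle row changes. The 6-month short placement is read from the paragraph structure and from the separate long-survey list.

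**Step 2. Formula.** Let f be the share of baseline respondents who take the long survey. Let p_L and p_S be the prevalence in long-survey and short-only participants. Assume no true change and that all baseline respondents answer at 6 months. Baseline shows p_L, and 6 months shows f·p_L + (1 − f)·p_S. The false change is therefore (1 − f)(p_S − p_L).

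**Step 3. Illustration for PHQ-9.** Assume GHQ-12 caseness of 50%, and PHQ-9 caseness of 45% in GHQ-12 cases and 7% in non-cases. True prevalence is 0.5 × 45 + 0.5 × 7 = 26.0% at both waves.

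- Uptake 60% in cases, 70% in non-cases: the case share among long-survey completers is 0.30/(0.30 + 0.35) = 0.4615. Observed baseline prevalence is 7 + 38 × 0.4615 = 24.5%, a false **rise of 1.5 points**.
- Uptake 50% and 75%: the case share is 0.25/(0.25 + 0.375) = 0.40. Observed baseline prevalence is 7 + 38 × 0.40 = 22.2%, a false **rise of 3.8 points**.
- Uptake reversed: 70% and 60% gives 27.5%, and 75% and 50% gives 29.8%, false **falls of 1.5 and 3.8 points**.
- Equal uptake: case share 0.50, prevalence 26.0%, false change **0**.

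Check of the second case against Step 2: f = 0.625, p_S = 7 + 38 × (0.25/0.375) = 32.3%, and 0.375 × (32.3 − 22.2) = 3.8.

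**Step 4. Unequal return at follow-up.** If long-survey completers are likelier to return, f in Step 2 is replaced by their larger share among 6-month respondents. With that share at 0.8 and the same prevalences, the second case falls to 0.2 × (32.3 − 22.2) = 2.0 points.

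**Step 5. Does a participant random intercept remove it?** One simulated dataset had 4,000 people, score SD 5, about 60% uptake and no true change:

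| Uptake depends on | Difference in wave means | Random-intercept model | Paired change |
|---|---|---|---|
| nothing | −0.06 | −0.02 | 0.00 |
| stable trait | −1.08 | −0.31 | +0.13 |
| baseline score | −1.43 | −0.80 | −0.45 |

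The random intercept reduces the artefact but does not remove it. The plan names observations and Trusts as levels 2 and 3 and does not name the participant. Paired change is close to zero when uptake follows the stable trait, but not when it follows the baseline score itself.

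**Step 6. Does weighting on GHQ-12 work?** In the first case of Step 3, inverse-uptake weights restore the case share to (0.30/0.60)/(0.30/0.60 + 0.35/0.70) = 0.50, and so 26.0%. This is true by construction, because uptake in that example depends on GHQ-12 status alone.

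**The case against.** The strongest reply is that the article specifies no change-from-baseline contrast for any of these scales. The longitudinal models target associations of sociodemographic and occupational factors with outcomes. The analysis of pressure on Trusts divides the baseline collection period, where the placement of baseline items is constant. Two of the three temporal hypotheses (baseline mental health and other predictors of follow-up mental health) are regressions on follow-up outcomes, not comparisons of wave means. GHQ-12 gives an unaffected trend. Weighting and analysis sets are also commonly left to a fuller document.

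Most of this stands as a limit on scope. A reader might infer that the plan treats all waves as if the same people had answered, or that every temporal hypothesis is compromised. The text supports neither. Restricting baseline MIES to long-survey completers shrinks the sample and may select it, but does not produce the false rise or fall computed here. Nor does the plan ignore the selection: it rakes on demographics and compares short-only with short-plus-long completers. And everyone was offered the long survey, so the difference lies in who opted in, not in who was asked.

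What does not stand is that this is merely unstated detail. The article fixes the outcomes, the three-wave models, the plots of all measures, the raking variables and the limit on imputation. Followed as written, nothing adjusts for distress-related uptake of the long survey, and the planned comparison of completers is descriptive.

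**Conclusion.** The mismatch in placement is in the text. For GAD-7, PHQ-9, AUDIT, PCL-6, MIES and the suicidality items, prevalence by wave, plots over time and time contrasts that use all available data can show false change if long-survey uptake is related to distress. The three-wave models name the five scales but not the suicidality items, which are exposed through the plots and any wave-by-wave summary.

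Under the stated assumptions the artefact in PHQ-9 prevalence is about 1.5 to 3.8 points in either direction. It is zero if uptake is unrelated to distress, and smaller if long-survey completers return more often. The article does not let a reader determine its size or sign, so it would be wrong to say that the trends will be biased by these amounts. The extension to 12 months rests on versions described only as similar.

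Not affected by the change of placement: GHQ-12, analyses of baseline responses within the baseline period, and the diagnostic interview component. The point should be fixed because the remedy is cheap, but it touches secondary time trends and does not undermine the study's main aims.

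**What to change.** Baseline data are already collected, so placement cannot change and the remedy lies in the analysis. For any comparison of these measures across waves, the plan should state one of the following:

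1. Weight baseline values by the inverse probability of completing the long survey, modelled on baseline GHQ-12 score and the other short-survey items (such as role, Trust and completion date) and combined with the existing raking weights.
2. Multiply impute the missing baseline scores of short-only participants, using baseline GHQ-12, the short-survey items and the person's own follow-up scores.

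Show paired change in participants with both values as a sensitivity analysis, with a note that this group can still be selected. Present the trend in GHQ-12 alongside, as the measure in the short survey at baseline and 6 months.

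Both methods assume that uptake is explained by the variables in the model. If it also depends on the unobserved baseline score, some bias remains, and the report should say so.

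The cost is a few sentences in the analysis plan, one extra weighting or imputation model, and slightly wider intervals for the baseline values of these measures.

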##### Follow-up—12 months

Similar short and long versions will be used in the 12-month follow-up survey as the 6-month survey, with further refinement as the pandemic evolves.

#### Diagnostic interview study

CIS-R will be used to assess mental disorders.^14^ The CIS-R is a standardised interview for use in general practice, community settings, hospitals and occupational contexts, and consists of 10 items, each scored on a scale of 0–4, with scores combined to provide a total weighted score. Questions refer to symptoms in the previous week. Use of the CIS-R allows comparison with a national probability sampled survey, the Adult Psychiatric Morbidity Survey.^25^

CAPS-5 will be used to assess PTSD.^16^ CAPS-5 is a structured interview for use in clinical and research settings that assesses symptom severity and diagnostic status of PTSD in line with Diagnostic and Statistical Manual of Mental Disorders, Fifth Edition (DSM-5) criteria. The tool consists of 30 items, on a 5-point rating system, across seven criteria that ask about symptoms within the past month; scores are combined to create a total symptom severity score and are used to establish presence or absence of the diagnosis.

#### Qualitative interview study

Semistructured interview schedules will be constructed using Normalisation Process Theory as a framework in order to address topics relevant to the evaluation and implementation of interventions.^26^ Questions will be included to draw out details about: how and why staff support programmes have been used, including ease of access and use; whether they have been helpful or unhelpful, and why; how information about such interventions could be communicated to staff most helpfully; and whether there are additional supports that would be helpful for Trusts to provide.

### Study procedures

#### Longitudinal cohort study

##### Recruitment

Potential participants will be identified via each Trust Human Resources system. Senior management at each site will use existing dedicated group email lists to circulate details of the study and the URL for the baseline survey of the longitudinal cohort study, emphasising the voluntary nature of participation. A ‘cascade’ of emails and contacts about the study will be encouraged in each Trust, via staff support teams/leads, chief nursing officers, medical directors, occupational health departments, Union representatives and well-being hub users. The study will be promoted during team briefings, included in Trust newsletters, highlighted by news items on Trust intranet websites, posted to closed social media groups, set by Information Technology (IT) services as screen-savers on Trust computers, and posters about the study will be displayed in staff rest areas and flyers added in ‘goodie’ bags for staff (in line with any necessary infection control guidelines). Participants will also be recruited via Trust influenza clinics.

In Nightingale Hospitals the study will be promoted, and its importance highlighted, by the staff health and well-being team leads at each site, as well as the chief nursing officer, medical director and other team leads involved.

##### Consent

Potential participants will be able to view the information sheet via the study website, then register and provide informed consent if they wish to complete the survey. Paper copies of the participant information sheet (PIS) and consent form can be provided on request. Questions can be emailed to the research team via a dedicated study email address. Participants will provide consent to take part in the study, including baseline and follow-up surveys, and can opt in to consent to be contacted about any linked future studies (eg, trials of support interventions). We will make clear that participation is voluntary and that participants can withdraw at any time without detriment. Due to the rapid publication of data summaries, it will not be possible to withdraw data from published work, but we will not use withdrawn data in any future publications.

##### Data collection

Baseline data were collected from April 2020 to January 2021. Staff completing the baseline survey will be invited to complete follow-up surveys at 6 months and 12 months after they have completed the baseline survey. All participants will be followed up at each subsequent data collection point, regardless of whether they completed the previous survey, unless they choose to withdraw from the study.

The online survey will be administered using Qualtrics survey software, hosted by King’s College London, and downloaded data will be pseudonymised and stored on secure servers at King’s College London and University College London.

#### Diagnostic interview study

##### Recruitment

Participants meeting the inclusion criteria will be emailed with an invitation to participate in the study, including the PIS. Participants who respond to the email indicating their interest will receive a follow-up email containing a link to a digital calendar where they can select an interview slot suitable to them using an assigned participant Identification (ID), which will be confirmed by email by the research team. Participants who do not select a time slot within 10 days of the booking emails being sent will be prompted to respond if still interested in participating, and followed up by phone calls or texts to confirm interest or withdrawal.

Participants will be able to email the research team via the dedicated study email address with any queries.

##### Consent

Participants will be sent the link to a Qualtrics survey, 1–3 days prior to their interview date, which will contain the online consent form in which they provide the phone number that the research team will call them on for the interview. Provided consent is given, the survey will continue to the administration of the GAD-7, PHQ-9, PCL-6 and GHQ-12.

The morning of the interview, a member of the research team will check completion of the survey; participants who have not started the survey, or who have consented to the study but not completed the measures will be prompted to complete the survey. If necessary, their interview will be rescheduled. Participants who have completed the survey will be send a reminder of their interview time.

##### Data collection

Interviews will be conducted over the phone by researchers based in a confidential location, with calls recorded on an encrypted audio recorder in case of a need for data verification. Researchers will manually enter responses to interview questions into a preprogrammed Qualtrics survey form, following the standard interview procedure for the CIS-R or the CAPS-5 depending on which group the participant belongs to.

Once the interview is complete, the interviewer will email the participant a £25 voucher to thank them for their time and log this payment in the contact database.

